## Abstract

**Background:**

Incisional hernia following abdominal surgery is a frequent complication of midline laparotomy. This complication is strongly associated with the technique and material used for suture. While a monofilament absorbable suture is recommended to prevent incisional hernia, it can lead to suture loosening or surgical-knot breakage. Although barbed sutures can be an alternative suture material in abdominal fascial closure, evidence for its safety and effectiveness is lacking. Therefore, we designed a prospective randomized trial to evaluate the safety and efficacy of absorbable barbed sutures for midline fascia closure in minimally invasive surgery for colorectal and gastric cancers in comparison with conventional absorbable monofilament sutures.

**Methods:**

A total of 312 patients who underwent minimally invasive surgery for colorectal and gastric cancers will be randomly allocated to either the absorbable barbed or monofilament suture group for abdominal fascia closure in a 1:1 ratio. The primary outcome is incisional hernia rate within 3 years after surgery, as verified by physical examination and computed tomography. Postoperative complications, including surgical site infection, postoperative pain, and quality of life, will be compared between two groups as secondary outcomes. The investigator will examine the patients until discharge and at 6, 12, 18, 24, and 36 months postoperatively.

**Discussion:**

This is the first randomized controlled trial to compare absorbable barbed sutures with monofilament sutures for midline fascia closure in minimally invasive surgery. If absorbable barbed sutures demonstrate superior results to those of monofilament sutures, this type of suture material may be recommended as an alternative option for abdominal fascia closure.

**Trial registration:**

KCT0007069. Registered on January 30, 2023

## Introduction

### Background and rationale {6a, 6b}

Laparoscopic and robotic surgery has become a preferred treatment option for colorectal and gastric cancers rather than open surgery because of its minimally invasive nature and short-term operative outcomes [1–5]. During minimally invasive gastrointestinal surgery, mini-laparotomy is used for extracorporeal anastomosis, specimen extraction, or single-port surgery. Midline incision is widely used for mini-laparotomy [6], because it is easy to perform, results in minimal blood loss, provides a better surgical view, and is more convenient for closure than other types of incision [7]. However, a midline incision carries a high incidence of incisional hernia [8].

Incisional hernia is a commonly encountered complication after abdominal surgery, with a reported incidence of 10–32% [9, 10]. Incisional hernia diminishes a patient’s quality of life due to pain and discomfort [11]. Although minimally invasive surgery with a smaller incision and limited abdominal wall trauma is expected to reduce incisional hernia, the incidence of incisional hernia of this approach did not differ from that of open surgery [12, 13]. Several methods of abdominal closure have been reported to prevent incisional hernia after abdominal surgery. A running technique with long-lasting monofilament suture material is recommended to prevent incisional hernia [14]. However, monofilament suture has the disadvantage of being easily loosening and requiring a surgical knot, resulting in a potential risk of incisional hernia [15].

Barbed suture is a new type of suture material, first patented in 1964. It consists of standard monofilament suture with tiny barbs along its length that are designed to anchor the suture without the need for knots [16]. These new materials have become popular for skin and uterine closures during cesarean section, orthopedic surgery, and gastrointestinal surgery due to reduced tissue trauma and convenience [17–20]. In animal experiments, barbed sutures for fascia closure showed adequate tensile strength [21]. However, they are yet to be clinically adopted owing to insufficient evidence of their safety and efficacy as compared to those of conventional suture materials. Therefore, we propose a randomized controlled clinical trial (Barbed trial) to compare the outcomes of absorbable barbed sutures and conventional absorbable monofilament sutures for midline fascia closure in minimally invasive surgery for colorectal and gastric cancers.

### Objective {7}

This study aimed to evaluate the safety and efficacy of absorbable barbed sutures for midline fascia closure in minimally invasive surgery for colorectal and gastric cancers in comparison with conventional absorbable monofilament sutures.

### Study design {8}

The Barbed trial is a prospective, superiority, single-center, randomized trial comparing the clinical outcomes of absorbable barbed sutures and monofilament sutures. A total of 312 patients will be enrolled and randomly allocated to use absorbable barbed or monofilament sutures for midline fascia closure in a 1:1 ratio. The surgical procedure used to close the midline fascia was standardized for both types of suture material. The investigator will examine the patients until discharge and at 6, 12, 18, 24, and 36 months postoperatively (Fig. 1). This study is ongoing at Jeonbuk National University Hospital and will last 3 years for each patient. This trial was registered with the Clinical Research Information Service of Korea.

**Fig. 1 Fig1:**
[figure not shown]
Control group : Absorbable monofilament suture

## Method: participants, interventions, and outcomes

### Study setting {9}

This study will enroll participants who are scheduled to undergo minimally invasive gastric or colorectal cancer surgery at Jeonbuk National University Hospital. This study was approved and supported by the Institutional Review Board of Jeonbuk National University Hospital (CUH 2021-09-040).

### Eligibility criteria {10}

#### Inclusion criteria

The inclusion criteria were as follows: (1) patients who were diagnosed with colorectal or gastric adenocarcinoma, (2) patients who underwent laparoscopic and robotic radical surgery, and (3) patients who were older than 20 years of age.

#### Exclusion criteria

Patients would be excluded if they fulfill any of the following exclusion criteria:Patients who underwent open surgeryPatients with possible distant metastasis in preoperative studiesPatients who underwent past abdominal surgeryPatients who had midline incision of less than 1 cm or longer than 10 cmPatients who had incision which is not located at the midlinePatients who underwent emergency operation, palliative surgery, or ileostomy or colostomy formationPatients with cancer-related complications (perforation or abscess)Patients who participated in another clinical trial within the past 6 months

### Who will take informed consent? {26a}

The trial details will be explained in full to potential participants by investigators, and an informed consent form will be provided. Adequate time will be given to participants to consider their decision regarding trial participation. Subsequently, participants can sign the informed consent and they can withdraw at any time during the trial.

### Additional consent provisions for collection and use of participant data and biological specimens {26b}

Not applicable as no participant data and biological specimens were collected in this study.

### Interventions

#### Intervention description {11a}

Surgical procedures are performed under general anesthesia and by an experienced surgeon. To achieve standardization of suture technique, we provide surgeons with formal video of fascial closure using two suture materials. The location of the midline incision, which is supra-, trans-, or infra-umbilical mini-laparotomy, is determined according to the surgeon’s preference. At the end of surgery, fascia closure is achieved with absorbable barbed sutures (Stratafix®, Ethicon Inc., USA) for the study group and absorbable monofilament sutures (Maxon®, Covidien Inc., USA) for the control group. In all cases, the suture-to-wound length ratio is at least 4:1 for closure of the midline incision, and the inter-suture spacing is less than 1 cm. We avoid mass closure, which is performed with a suture bite, including all layers of the abdominal wall, except the skin. A single aponeurotic closure is applied to the midline incision in both groups. Subcutaneous tissue closure is not mandatory in this study. The skin can be approximated by using staples.

#### Criteria for discontinuing or modifying allocated interventions {11b}

There are no predetermined criteria for discontinuing or modifying the intervention assigned to participants. All individuals are participating on a voluntary basis, and they have the option to withdraw from the study at any time for any reason without facing any negative consequences.

#### Strategies to improve adherence to interventions {11c}

We will recruit patients who are scheduled to undergo surgery for gastric or colorectal cancer. By enrolling participants who require regular cancer screening, we anticipate that adherence to the study protocol will improve. Furthermore, participants will be informed of the significance of completing follow-up assessments.

#### Relevant concomitant care permitted or prohibited during the trial {11d}

All participants will receive standard postoperative management after surgery for gastric or colorectal cancer. For patients with wound infection, commercial dressing preparations or negative pressure wound therapy will be permitted.

#### Provisions for post-trial care {30}

There will be no provision for patients who participate in the trial. Post-trial care will follow the standards of care after gastric and colorectal cancer surgery.

### Outcomes {12, 18a}

#### Primary outcome

The primary outcome of this trial is the frequency of incisional hernia 3 years after surgery. We use the definition of incisional hernia according to the European Hernia Society: “any abdominal wall gap with or without bulge in the area of a postoperative scar perceptible or palpable by clinical examination or imaging” [22]. All patients will be examined using computed tomography to evaluate cancer recurrence during the study period. Therefore, the investigator will examine the occurrence of incisional hernia through physical examination and computed tomography scans at 6, 12, 18, 24, and 36 months after surgery in the outpatient clinic.

#### Secondary outcomes

Postoperative complications, including surgical site infection (SSI), pain, and quality of life, will be compared between the absorbable barbed suture and conventional absorbable suture groups.

Postoperative complications is defined as any adverse events that required additional pharmacological, interventional, or surgical management within 30 days after surgery. All postoperative complications were graded according to the Clavien-Dindo classification [23]. SSI is defined according to the criteria of the Centers for Disease Control and Prevention [24]. We divided SSI into superficial, deep incisional, and organ/space-related types occurring within 30 days after surgery. We will evaluate postoperative pain on postoperative days 1, 2, and 3 using a numeral rating scale. The verbal numeral rating scale ranged from 0 to 10 (0 = no pain and 10 = worst pain). To analyze the quality of life, the SF-36 and body image questionnaire will be used and documented by the patient 12 months postoperatively (Fig. 2). All outcomes will be evaluated by the investigators and they are specially trained for reliability.

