### Participant timeline {13}

The participant timeline is shown in Fig. 2.

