### Recruitment {15}

Patients who are scheduled to undergo minimally invasive gastric or colorectal cancer surgery will be considered as candidates for trial enrolment in concordance with the inclusion and exclusion criteria. Informed consent will be obtained from all participants by investigators. We are confident that we can enroll a sufficient number of eligible patients, as our institution conducts over 150 surgeries for gastric cancer and 300 surgeries for colorectal cancer annually.

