## Assignment of interventions: allocation

### Sequence generation {16a}

Eligible patients will be randomly allocated to use absorbable barbed or monofilament sutures for midline fascia closure in a 1:1 ratio. Stratified randomization was performed by medical statisticians who do not participate in this study. This randomization is based on an independent, computer-based sequence generated from the implementation of the dynamic algorithm with the cancer types as the stratifying variables.

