## Assignment of interventions: blinding

### Who will be blinded {17a}

After the interventions are assigned, participants will be blinded. The results will be kept confidential from the participants throughout the entire trial. Surgeons will not be blinded because the intervention involves a surgical procedure.

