## Statistical methods

### Statistical methods for primary and secondary outcomes {20a}

A planned analysis will be performed after all patients have completed their 3-year follow-up. Categorical variables will be presented as numbers with percentages, and continuous variables will be presented as means with standard deviations or medians with interquartile ranges. The analysis will be performed using the intention-to-treat approach. The primary outcome will be analyzed using chi-squared and Kaplan-Meier tests. Risk factors for incisional hernia will be analyzed using the Cox regression analysis. Secondary outcomes will be tested using the chi-squared test for categorical variables and the *t*-test or Mann-Whitney test for continuous variables, as appropriate. The level of statistical significance will be set at *p* < 0.05.

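### The 12-month SF-36 and body image scores are compared by an unadjusted two-sample test, which is unbiased but less precise than an analysis of covariance on cancer type and any preoperative score

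*Protocol article*

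**What the plan says.** Secondary outcomes gives one time for quality of life: "the SF-36 and body image questionnaire will be used and documented by the patient 12 months postoperatively". That sentence refers to Fig. 2, and Participant timeline {13} adds only: "The participant timeline is shown in Fig. 2". The figure is not reproduced in the text at hand. The stated purpose is a comparison between arms: quality of life, among other outcomes, "will be compared between the absorbable barbed suture and conventional absorbable suture groups". No change from baseline is named as an endpoint.

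For continuous secondary outcomes, Statistical methods {20a} names "the *t*-test or Mann-Whitney test for continuous variables, as appropriate". It names no covariate. Sequence generation {16a} makes cancer type the stratifying variable of a dynamic allocation algorithm. Recruitment {15} says: "Patients who are scheduled to undergo minimally invasive gastric or colorectal cancer surgery will be considered as candidates for trial enrolment". Patients are therefore known to the investigators before the operation.

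**The concern.** SF-36 scores one year after gastric or colorectal cancer surgery vary widely between patients for reasons unrelated to the suture, such as health before surgery, cancer type and later treatment. An unadjusted test leaves all of this variation in the error term. Two sources could be taken out. Cancer type is recorded for everyone and was used to balance the arms. The preoperative score is either already collected (if Fig. 2 says so) or could be collected between consent and randomisation. Because allocation balances cancer type, a test that ignores it also tends to report a standard error that is somewhat too large.

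At stake is the precision of one secondary comparison. A real but modest difference in quality of life could be missed, and a chance imbalance in preoperative quality of life could be neither seen nor adjusted for if no such score is taken.

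**Working it through.** **The plan's own figure.** Sample size {14} concerns hernia only: 15% against 5%, two-sided α 0.05, power 80%. With pooled variance under the null and mean proportion 0.10:

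n = [1.960·√(2·0.10·0.90) + 0.842·√(0.15·0.85 + 0.05·0.95)]² / 0.10² = (0.832 + 0.352)² / 0.01 ≈ 140.1, hence 141 per group.

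This reproduces the stated 141. For 10% dropout, 141/0.9 gives 157 per group (314 in total) against the stated 156 (312), a trivial difference. No sample-size figure is given for quality of life, so nothing below changes the trial's size.

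**Unadjusted comparison.** The difference detectable with 80% power, in standard deviations (SD) of the score, is (1.960 + 0.842)·√(2/n). At n = 141 it is 0.334 SD; at n = 156 it is 0.317 SD.

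**Adding a preoperative score.** Let r be the correlation between preoperative and 12-month score. Analysis of covariance multiplies the variance of the arm difference by 1 − r², and the detectable difference by √(1 − r²). The documents give no r, so a range is assumed. The table takes 141 per group, all with a preoperative score; the last column assumes a true difference of 0.3 SD.

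| r (assumed) | Variance factor | Reduction | Equivalent patients (×) | Detectable difference | Power at 0.3 SD |
|---|---|---|---|---|---|
| 0 (as for unadjusted) | 1.00 | 0% | 1.00 | 0.334 SD | 71% |
| 0.3 | 0.91 | 9% | 1.10 | 0.318 SD | 75% |
| 0.5 | 0.75 | 25% | 1.33 | 0.289 SD | 83% |
| 0.7 | 0.51 | 49% | 1.96 | 0.238 SD | 94% |

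**Scores for only part of the patients.** If a fraction f has a preoperative score and the rest enter with a missing-baseline indicator, the average variance factor is about f(1 − r²) + (1 − f) = 1 − f·r². The overall reduction is then f·r². For r from 0.3 to 0.7 this is about 2% to 12% at an assumed f = 0.25, and about 5% to 25% at f = 0.5. The documents do not say how many patients were still to be enrolled.

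**Change scores.** Subtracting the preoperative score gives the variance factor 2(1 − r): 1.4, 1.0 and 0.6 at r = 0.3, 0.5 and 0.7. Below r = 0.5 that is worse than the plan's present test (power 57% at r = 0.3, against 71%). The gain comes from covariance adjustment, not from analysing change.

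**Cancer type alone.** Take Recruitment {15} (over 150 gastric and 300 colorectal operations a year) as a rough guide to the mix, about 1/3 to 2/3. If mean scores differ by δ within-group SD between cancers, cancer type explains (2/9)δ² / [1 + (2/9)δ²] of the variance. That is 0.9% for an assumed δ = 0.2 and 5.3% for δ = 0.5: a small gain, but one that needs no new data.

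**The case against.** The strongest objection is that the schedule is in the one place that cannot be read. The sentence on SF-36 points to Fig. 2, and a preoperative form may well be listed there. A reader might infer from the text that no preoperative measurement is taken; the documents do not establish that. This objection stands, and it makes the first step a check of Fig. 2. It does not remove the point about the analysis: if a preoperative score exists, the test named in Statistical methods {20a} leaves it unused.

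A reader might also fault the plan because it cannot show change within patients. It does not set out to. It promises a comparison between arms, allocation is randomised 1:1, and "After the interventions are assigned, participants will be blinded". A 12-month comparison of such arms is unbiased without any baseline.

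It would likewise be too strong to say that patients without a 12-month score leave nothing to impute from, or that nothing can be adjusted for without a baseline. Cancer type, pain on days 1 to 3, 30-day complications and any hernia examination before dropout are all collected. They can serve the multiple imputation foreseen in {20c} when more than 5% of a variable is missing. What would be absent is an earlier score on the same scale. Nor would a preoperative score settle how deaths before 12 months should be handled.

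Finally, covariates are often left to the statistical analysis plan, which is not shown. That is fair, but the article does more than stay silent: it names the tests. If the analysis plan already adjusts, the two need only be aligned.

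**Conclusion.** The point holds as a minor one about efficiency. On the readable text, the quality-of-life comparison is valid but less precise than it need be, because it ignores the stratification factor and any preoperative score. The 9% to 49% reduction in variance rests on an assumed correlation of 0.3 to 0.7 and applies only among patients who have a preoperative score; if the correlation is near zero, the gain is nil. For body image the correlation is even less certain, since some items may not apply before surgery. The gain from cancer type alone is probably a few per cent at most.

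The documents do not support a reading that the baseline is certainly absent, that the comparison is biased, or that the plan fails an aim of its own. Quality of life carries no sample-size claim, and the primary outcome is not affected.

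**What to change.** 1. **Check Fig. 2 or the full protocol** for a preoperative SF-36 or body image form. If there is one, name it under Secondary outcomes.
2. **In Statistical methods {20a}**, compare 12-month SF-36 and body image scores by analysis of covariance, with cancer type as a covariate for all patients and the preoperative score where one exists. If the scores are clearly skewed, keep the Mann-Whitney test as a sensitivity analysis. This costs nothing in data collection, but should be fixed before arm-level data are seen.
3. **If Fig. 2 shows no preoperative SF-36**, add one between consent and randomisation for patients still to be enrolled, together with those body image items that make sense before surgery. Candidates are identified while awaiting the operation, so no extra visit appears necessary. For patients already enrolled, use a missing-baseline indicator. This is acceptable because a value due before randomisation is missing independently of arm.
4. **In the missing-data section {20c}**, include the preoperative score, where available, in the imputation model.

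The cost is one questionnaire per remaining patient. Trial status gives the first recruitment as December 24, 2021 and the expected end as December 2023, so step 3 helps only as far as enrolment is still open. If it has closed, steps 1 and 2 remain, with step 4 for any scores that exist.

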**Fig. 2 Fig2:**
[figure not shown]
Experimental group : Absorbable barbed suture

### Participant timeline {13}

The participant timeline is shown in Fig. 2.

### Sample size {14}

We mainly have used absorbable monofilament sutures for fascia closure, and the overall incidence of incisional hernia was about 15%. Barbed suture began to be used for fascial closure in August 2020 during colorectal surgery. Before this randomized controlled trial, we conducted a pilot study of barbed suture for fascia closure. A total of 60 patients underwent fascia closure with barbed suture during laparoscopic colorectal surgery, and incisional hernia occurred in 2 patients (3.3%) within 1 year after surgery. Assuming additional patients with an incisional hernia during follow-up period, we determined possible incisional hernia rate to 5% in the barbed suture group for 3 years after surgery. Therefore, we hypothesized that the incidence of incisional hernia at 3 years after surgery will be lower in the barbed suture group than in the monofilament suture group. The sample size was calculated on the basis of this analysis plan, assuming that the incisional hernia rate of the barbed suture and monofilament groups at 3 years after surgery will be 5% and 15%, respectively. We calculated that 141 patients per group needed to achieve a two-sided α of 0.05 and statistical power of 80% using a chi-squared test. Assuming a 10% dropout rate, it is necessary to recruit 312 patients. Finally, 156 patients were assigned to the barbed suture and monofilament groups. The calculations were performed using G*Power 3.1.

